## Background

Idiopathic pulmonary fibrosis (IPF) is a chronic respiratory disease characterized by progressive scarring and architectural distortion of the lung parenchyma [1]. Patients with IPF have high morbidity, poor quality of life, and an average survival of 3–5 years from diagnosis [2]. There are only two Food and Drug Administration (FDA)-approved treatments for IPF in the United States, pirfenidone and nintedanib. Both drugs slow disease progression and have been linked to reduced mortality [3–5]. However, neither pharmacologic therapy reverses fibrosis or improves patient symptoms, and both drugs carry a significant side effect profile, making them poorly tolerated by a significant proportion of patients. Therefore, there is a continued, urgent, unmet need for more effective and better tolerated therapies for IPF.

In this protocol paper, we describe the design and rationale of the Phase III, multi-center randomized, double-blind, placebo-controlled Prospective Treatment Efficacy in IPF Using Genotype for NAC Selection (PRECISIONS) clinical trial. We highlight the novel approach of this trial to patient selection, by identifying individuals that carry a specific genetic variant, *TOLLIP* rs3750920 TT genotype, who are most likely to benefit from *N*-acetylcysteine (NAC) therapy. The PRECISIONS trial is one of the first studies to use a precision medicine approach in IPF, by testing the efficacy of a therapy in a targeted population based on a specific genotype.

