### Study overview

PRECISIONS is a multi-center, randomized, double-blind, placebo-controlled trial of 200 participants with TOLLIP rs3750920 TT genotype to receive NAC or placebo for a 24-month duration. The structure of the study is shown in Fig. 1. Study participants will be randomized to NAC or placebo in a 1:1 fashion, while receiving standard of care. Standard of care is defined as allowing background therapy with FDA-approved medications for IPF, such as pirfenidone or nintedanib, if taking a stable dose for at least 6 weeks prior to enrollment. Randomization will be stratified by stable concomitant IPF therapy use (pirfenidone or nintedanib) versus no pirfenidone or nintedanib use. A schematic overview of the study design is shown in Fig. 1.

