If there is more than 10% loss to-follow-up, sensitivity analyses will be performed based on multiple imputation of the primary outcome. If more than 10% of participants having missing adjustment variables for the secondary analyses of the primary endpoint, then sensitivity analyses multiply imputing the missing predictors will be performed. In the event more than 10% of participants switch concomitant therapy use after randomization (ex. participant who was not using pirfenidone at start of trial starts using pirfenidone mid-way through the trial), a sensitivity analyses will be performed that uses inverse weighting methodology.

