### Sample size and power calculation

It is anticipated that the event rate in the placebo arm will be highly dependent on the proportion of patients enrolled at different Gender, Age, and Physiology (GAP) scores [37]. The GAP index score will likely be heavily weighted towards 3 given the availability of pirfenidone and nintedanib. Assuming an exponential distribution for the composite endpoint comparable to that from the PANTHER study, we conservatively estimate a placebo yearly event rate to be 24% for the primary composite endpoint in participants not taking concomitant therapy [11]. We have also taken into account concomitant IPF therapy and conservatively estimate that 65% of the study population will be taking one of the two anti-fibrotic medications approved for treatment. We estimate the placebo event rate among participants taking concomitant IPF medications will be lower at a 12% yearly even rate. The estimate of the magnitude of the treatment effect is based on the PANTHER pharmaco-genetic study of the *TOLLIP* TT genotype, in which the primary endpoint was also a composite endpoint (decline of at least 10% in FVC, lung transplantation, hospitalization, and/or time to death) [13]. The hazard ratio was 0.14 in the PANTHER cohort and 0.23 in the validation cohort, both of which are large effect estimates. Given the retrospective and observational nature of this study, we took a very conservative approach in estimating the treatment effect. The estimate effect size for PRECISIONS is a 66.7% event reduction between NAC and placebo. Based on these estimates and a 10% dropout rate, we plan to enroll 200 randomized participants, which will provide 90.1% power assuming a two-sided type-I error rate of 0.05. Table 3 summarizes the power estimates for various event rates and treatment effects.

**Table 3 Tab3:** Statistical power assuming various event rates and treatment effects

Placebo event rate (%)	NAC event rate* (%)	Event rate reduction (%)	Power** (%)
24	6.0	75	97.5
30	7.5	75	99.3
36	9.0	75	99.8
24	8.0	66.7	90.1
30	10.0	66.7	96.0
36	12.0	66.7	98.7
24	12.0	50	62.3
30	15.0	50	73.1
36	18.0	50	80.6

*12-month event rates for the 35% of patients not taking concomitant IPF medication. The remaining 65% are assumed to have half the shown event rate in each arm based on taking IPF concomitant medication

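### The trigger for the antifibrotic-switching sensitivity analysis pools both arms and both baseline strata, so it cannot detect unequal starting of antifibrotics among the roughly 70 participants untreated at entry

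*Protocol article*

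**What the plan says.** In the protocol article, the section on analysis of the primary endpoint deals with switching in one sentence. "In the event more than 10% of participants switch concomitant therapy use after randomization", then "a sensitivity analyses will be performed that uses inverse weighting methodology". The example given is a "participant who was not using pirfenidone at start of trial starts using pirfenidone mid-way through the trial". No arm or baseline stratum is named in the trigger.

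Three other places bear on it:

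- **Study overview.** "Randomization will be stratified by stable concomitant IPF therapy use (pirfenidone or nintedanib) versus no pirfenidone or nintedanib use". This is therapy at entry.
- **Analysis of the primary endpoint.** Concomitant therapy is a subgroup variable and a covariate in the multivariable model. Neither is described as varying over time.
- **Sample size and power calculation.** The authors "conservatively estimate that 65% of the study population will be taking one of the two anti-fibrotic medications approved for treatment", which leaves 35% untreated. They assume a placebo yearly event rate of 24% without antifibrotics and 12% with them.

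**The concern.** The design assumes that antifibrotic use goes with half the event rate. On that assumption, starting one during follow-up is a strong co-intervention. What matters for interpreting the result is whether starts differ between arms, and starting from no therapy is possible only in the untreated 35%. A count pooled over arms and strata does not measure that difference. It is the same for 18 placebo and 2 NAC switchers as for 10 and 10, and in both cases (20 of 200) the analysis is not run.

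If NAC works, placebo participants may start antifibrotics more often, which would pull the arms together. With a null or borderline result, readers would want to know whether that had happened. Under the stated rule the weighted analysis that addresses it may not be run.

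**Working it through.** **Inputs (protocol article).** N = 200, allocated 1:1; 65% on antifibrotics at entry; placebo yearly rates 24% (untreated) and 12% (treated); a 66.7% reduction on NAC, so 8% and 4%; 10% dropout; 24 months; exponential times; log-rank test at two-sided 0.05.

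**Reproducing the plan's power.** The stated figure is 90.1%. A simulated log-rank test with the 35/65 mixture (4,000 runs) gives 90.2% if 10% are lost at baseline, 90.2% with 10% dropout per year and 92.2% with 10% dropout over two years. The plan's figure is reproduced.

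**How far the trigger reaches.**

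- Largest number of switchers that leaves it unmet: 0.10 × 200 = 20.
- Untreated stratum: 0.35 × 200 = 70, so 35 per arm.
- Twenty starters as a share of the stratum: 20/70 = 29%.
- Share of its placebo half: 10/35 = 29% with a 10:10 split, 15/35 = 43% with 15:5, 20/35 = 57% with 20:0.
- After the possible increase of 40 participants (N = 240), the 20:0 share is unchanged: 24/42 = 57%.
- If 60% are treated at entry, the 20:0 share is 20/40 = 50%. If 75% are, it is 20/25 = 80%.

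**Where the events come from.** With hazard λ = −ln(1 − yearly rate) and dropout hazard δ = −ln(0.9)/2 per year, the expected events among n participants are n × λ/(λ+δ) × (1 − exp(−2(λ+δ))).

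| Stratum at entry | Placebo | NAC | Total |
|---|---|---|---|
| Untreated (35 per arm) | 14.1 | 5.1 | 19.2 |
| Treated (65 per arm) | 13.9 | 4.8 | 18.8 |

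The untreated 35% supply about half of the 38 expected events.

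**Effect on power.** Two assumptions are added that the article does not state. Twenty untreated participants start an antifibrotic at month 4 if still event-free, and their yearly rate then falls to the treated-stratum rate of their own arm. With 10% dropout over two years and 20,000 runs per case:

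| Starters, placebo:NAC | Simulated power |
|---|---|
| none | 92.3% |
| 10:10 | 90.7% |
| 15:5 | 86.9% |
| 20:0 | 82.8% |

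Separate runs of the same cases gave 93%, 91%, 87% and 82%, so differences of a point are simulation and set-up noise. None of these cases sets off the trigger. Part of the loss, including all of it in the 10:10 case, comes from fewer events and not from imbalance.

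**The case against.** **The primary result is not invalidated. This stands.** The objective is NAC plus standard care against placebo plus standard care, and standard care allows antifibrotics. Under that comparison, more antifibrotic use on placebo is part of what is estimated. Only a supportive analysis is at issue.

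**The large figures are corner cases. This stands.** The 57% share and the 82–83% power need every switch in the trial to be an untreated placebo participant starting therapy. The trigger's wording plausibly also counts stops and drug changes among the 130 treated participants, and the Background describes the approved drugs as having side effects "making them poorly tolerated by a significant proportion of patients". Such switches would bring the count past 20 sooner. Many starts prompted by worsening would also follow the primary event, since 10% FVC decline and respiratory hospitalisation are themselves components, and would leave the result untouched. The simulation ignores this and so tends to overstate the loss.

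**A reader might infer a risk of false benefit.** If NAC had no effect and all 20 starters were on NAC, a significant result favouring NAC would occur in roughly 7% of trials, not 2.5%. The documents do not support this as a concern. With starts unrelated to arm, all 20 of 70 falling in one named arm has a probability of about 2 in 100 million (hypergeometric, 35 per arm). A split of 15:5 or more extreme towards NAC has a probability of about 0.8%. In a blinded trial nothing in the article suggests another mechanism.

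**A reader might also infer that counting post-event switches causes the check to be missed.** It does the reverse: it makes the trigger fire sooner. It is only a reason to count the relevant switches.

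**The full analysis plan may tabulate switching anyway.** It may, and its absence from an article is no finding. The trigger itself, however, is fixed in the article.

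**A threshold avoids imprecise weighted estimates.** That is a fair reason for having one, but not for pooling it over arms and strata.

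**Conclusion.** The point holds as a weakness in a stated rule for a supportive analysis. The pooled count cannot see the between-arm difference that gives the analysis its purpose, and up to 20 starters (29% of the untreated stratum, 43% of its placebo half at 15:5) can pass without it. Power falls by about 2 points for a balanced 20, about 5 to 6 for 15:5 and about 10 at the 20:0 extreme.

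These sizes rest on the plan's 35/65 split and event rates, on starts at month 4, on the full halving of the rate applying to starters, and on no other switches in the trial. Neither an invalid primary test nor a material rise in type I error follows. Severity: consider.

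**What to change.** 1. Always tabulate antifibrotic starts, stops and changes that occur before the first primary event, by arm and by baseline stratum.
2. Run the already planned inverse-weighted sensitivity analysis on those pre-event switches without the pooled 10% condition. If a threshold is preferred, set it by arm within the untreated stratum; 10% of 35 would be exceeded at 4 starters in an arm.
3. Leave the primary log-rank analysis unchanged.

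The cost is a change of wording and one analysis that is already specified. Concomitant medication is reviewed at every visit from enrolment and at the monthly calls (Table 2), so no new data are needed. The downside is that the weighted estimate will be imprecise when switchers are few, which the tabulation will make plain.

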### Analysis of secondary and exploratory endpoints

The analyses for time-to-event secondary and exploratory endpoints will be similar to those outlined for the primary endpoint. Rate endpoint analyses will be based on univariable and multivariable zero-inflated negative binomial regression models. Analyses of trajectory endpoints will use a repeated measure approach that uses mixed models and incorporates all available assessments from randomization through 24 months. In order to examine the sensitivity and specificity of home spirometry values in predicting subsequent primary and secondary time-to-event outcomes, an exploratory receiver operating characteristic analysis will be performed.

### Sample size and power calculation

It is anticipated that the event rate in the placebo arm will be highly dependent on the proportion of patients enrolled at different Gender, Age, and Physiology (GAP) scores [37]. The GAP index score will likely be heavily weighted towards 3 given the availability of pirfenidone and nintedanib. Assuming an exponential distribution for the composite endpoint comparable to that from the PANTHER study, we conservatively estimate a placebo yearly event rate to be 24% for the primary composite endpoint in participants not taking concomitant therapy [11]. We have also taken into account concomitant IPF therapy and conservatively estimate that 65% of the study population will be taking one of the two anti-fibrotic medications approved for treatment. We estimate the placebo event rate among participants taking concomitant IPF medications will be lower at a 12% yearly even rate. The estimate of the magnitude of the treatment effect is based on the PANTHER pharmaco-genetic study of the *TOLLIP* TT genotype, in which the primary endpoint was also a composite endpoint (decline of at least 10% in FVC, lung transplantation, hospitalization, and/or time to death) [13]. The hazard ratio was 0.14 in the PANTHER cohort and 0.23 in the validation cohort, both of which are large effect estimates. Given the retrospective and observational nature of this study, we took a very conservative approach in estimating the treatment effect. The estimate effect size for PRECISIONS is a 66.7% event reduction between NAC and placebo. Based on these estimates and a 10% dropout rate, we plan to enroll 200 randomized participants, which will provide 90.1% power assuming a two-sided type-I error rate of 0.05. Table 3 summarizes the power estimates for various event rates and treatment effects.

**Table 3 Tab3:** Statistical power assuming various event rates and treatment effects

Placebo event rate (%)	NAC event rate* (%)	Event rate reduction (%)	Power** (%)
24	6.0	75	97.5
30	7.5	75	99.3
36	9.0	75	99.8
24	8.0	66.7	90.1
30	10.0	66.7	96.0
36	12.0	66.7	98.7
24	12.0	50	62.3
30	15.0	50	73.1
36	18.0	50	80.6

*12-month event rates for the 35% of patients not taking concomitant IPF medication. The remaining 65% are assumed to have half the shown event rate in each arm based on taking IPF concomitant medication

**Power estimates assume censorship/dropout rate of 10% for the NAC vs placebo comparison in 200 randomized participants. Calculations assume a 2-sided Type-I error rate of 0.05. Follow-up is planned to be 24 months for all patients. Power calculations were based on a log-rank test with assumed event rates following an exponential distribution

An interim sample size adjustment is also incorporated into the statistical analysis plan. Upon enrollment of at least 25 placebo participants with at least 12 months of follow-up, an interim sample size adjustment analysis will be performed. If the observed one-year event rate in this group of placebo participants is below 16%, the sample size will be increased by 40 participants to maintain at least 80% power for the study assuming a 66.7% event rate reduction in the NAC arm compared with placebo. No type I error would be spent as part of this analysis because the adjustment would not take into account the event rate in the NAC arm. This approach is a precaution that protects study power in the case of the placebo arm event rate being below the range anticipated in the design of the trial.

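### The interim rule promises at least 80% power from a fixed 40 extra participants at any placebo rate below 16%, but 240 participants give only about 60–70% at the lower rates

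*Protocol article*

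**What the plan says.** All of this is in the Protocol article, section Sample size and power calculation, including Table 3 and its notes.

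- **Rule.** Once at least 25 placebo participants have at least 12 months of follow-up, their one-year event rate is compared with 16%. If it is lower, "the sample size will be increased by 40 participants to maintain at least 80% power for the study assuming a 66.7% event rate reduction".
- **Purpose.** "This approach is a precaution that protects study power in the case of the placebo arm event rate being below the range anticipated".
- **Power model.** "Power calculations were based on a log-rank test with assumed event rates following an exponential distribution". "Calculations assume a 2-sided Type-I error rate of 0.05". Follow-up is 24 months for everyone and dropout is 10%.
- **Placebo rates.** "we conservatively estimate a placebo yearly event rate to be 24% for the primary composite endpoint in participants not taking concomitant therapy". For the rest, "We estimate the placebo event rate among participants taking concomitant IPF medications will be lower at a 12% yearly even rate". The authors "conservatively estimate that 65% of the study population will be taking one of the two anti-fibrotic medications approved for treatment". The Table 3 note carries the halving through every row: "The remaining 65% are assumed to have half the shown event rate in each arm based on taking IPF concomitant medication".
- **Base case.** 200 participants and a 66.7% reduction give 90.1% power. The lowest off-antifibrotic placebo rate in Table 3 is 24%, and no power is given for 240 participants.

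**The concern.** The rule has one trigger, one size of increase and a guaranteed minimum power, with no lower limit on the placebo rate. For a fixed sample size and a fixed relative reduction, expected events and therefore power fall as the placebo rate falls. A fixed step can meet 80% at one rate and above it, but not at every rate below a threshold.

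The rates where the guarantee fails are low ones, and the safeguard exists for low rates. The sponsor and the DSMB could believe that a low-event trial expanded to 240 is adequately powered. A null result could then be over-read as evidence against NAC in the TT genotype. Because Table 3 stops at 24%, a reader of the article cannot see the shortfall.

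**Working it through.** **Inputs (all from the sample-size section, except 1:1 allocation from Study overview).** 35% off antifibrotics at yearly placebo rate r; 65% on antifibrotics at r/2; NAC rates one third of placebo; 24 months of follow-up; 10% dropout; two-sided 5% log-rank test. Assumption: dropout is exponential and reaches 10% over the 24 months.

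**Formulas.** The hazard is λ = −ln(1 − rate) and the dropout hazard is μ = −ln(0.9)/2 = 0.0527. The probability of an observed event is λ/(λ+μ) × [1 − exp(−2(λ+μ))]. Expected events are D = (N/2)(P + Q), where P and Q are the 35/65 mixtures for placebo and NAC. The marginal hazard ratio is HR = ln(1 − whole-arm NAC rate)/ln(1 − whole-arm placebo rate). Freedman power is Φ(√D × (1 − HR)/(1 + HR) − 1.96).

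**Step 1: reproduce the printed 90.1% (r = 24%, N = 200).**
- P = 0.35 × 0.4028 + 0.65 × 0.2146 = 0.2805
- Q = 0.35 × 0.1460 + 0.65 × 0.0745 = 0.0995
- D = 100 × 0.3800 = 38.0
- HR = ln(1 − 0.054)/ln(1 − 0.162) = 0.314
- √38.0 × 0.686/1.314 − 1.96 = 1.26, so power is 89.6%

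Three other methods give 88.1% (normal test of the log hazard ratio with variance 1/d₁ + 1/d₂, the expected events per arm), 91.0% (two proportions at 24 months) and about 92% (simulated log-rank tests). Freedman and two proportions both match all nine rows of Table 3 to within 2 points, so the model is the article's.

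**Step 2: same model at N = 240, 66.7% reduction.** For r = 12%: P = 0.1470, Q = 0.0505, D = 120 × 0.1975 = 23.7, HR = 0.324, and √23.7 × 0.676/1.324 − 1.96 = 0.53, so power is 70.0%. The whole-arm rate is 0.35r + 0.65r/2 = 0.675r.

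| Placebo rate, off / on antifibrotics | Whole arm | Events | Freedman | Log-HR variance | Two proportions | Simulated log-rank |
|---|---|---|---|---|---|---|
| 16% / 8% | 10.8% | 31.2 | 81.9% | 79.3% | 83.1% | 85% |
| 14% / 7% | 9.45% | 27.5 | 76.6% | 73.6% | 77.7% | 80% |
| 12% / 6% | 8.1% | 23.7 | 70.0% | 66.8% | 71.0% | 72–74% |
| 10% / 5% | 6.75% | 19.9 | 62.1% | 58.7% | 62.8% | 64–65% |

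**Step 3: both readings of the 16%.** The article does not say which scale it is on.
- *Off-antifibrotic rate, as in Table 3.* Power at 240 is about 80% at the trigger. It crosses 80% somewhere between about 14% and just over 16%, depending on the method, and is lower for the rest of the range.
- *Whole-arm rate.* Freedman and two-proportion power at 240 is 93.9–94.9% at 16%, 85.7–87.0% at 12%, 82.6–83.8% at 11%, 78.9–80.1% at 10%, 74.6–75.6% at 9%, 69.5–70.4% at 8% and 63.7–64.4% at 7%. Simulation gives 82% at 10%, 77–78% at 9% and 72% at 8%. The floor fails below roughly 9.5–11%.

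The Schoenfeld formula overshoots the printed base case (94.6% against 90.1%). Even so, it drops below 80% at a whole-arm rate of 8% (77.8%).

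**The case against.** The strongest reply is that the whole-arm reading is the literal one, since 16% is compared with the rate in the placebo participants without restriction. On that scale 240 participants keep at least 80% from 16% down to about 10%. The planned whole-arm rate is 0.35 × 24% + 0.65 × 12% = 16.2%, so power of 60–70% arises only at about half the planned rate or less. This is correct and limits where the promise fails. It does not supply the missing lower bound.

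Second, the trigger uses an observed rate in as few as 25 people, not the true rate. With exactly 25, below 16% means three or fewer events. At a true rate of 16.2% that happens 41% of the time, and 240 then gives about 95% power. So firing does not by itself mean the trial is underpowered. But at a true rate of 8.1% the rule fires 86% of the time and leaves power near 70%.

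Third, simulated log-rank power runs above the closed forms, so 12%/6% may be nearer 72–74% than 70%. Simulation also runs about 2 points above the printed base case, and every method falls below 80% there.

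Fourth, the DSMB sees data by arm at least twice a year and can recommend changes, and a null result should be judged on its confidence interval. That softens the consequence but does not make the stated figure right.

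The fuller plan may contain more detail, but the numerical guarantee is printed in the article and fails on the article's own inputs.

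**Conclusion.** The concern holds. A fixed increase to 240 does not secure 80% power for every placebo rate below 16%. It does so down to a whole-arm one-year placebo rate of roughly 9.5–11%, or about 14–16% on the off-antifibrotic scale. Power is then 67–74% at 12%/6% and 59–65% at 10%/5%, which is a 26–41% chance of missing the assumed 66.7% reduction. The floor fails on either scale of the trigger: almost at once on the Table 3 scale, and only at clearly lower rates on the whole-arm scale.

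This rests on the 65% antifibrotic share, the on-antifibrotic rate staying at half the off-antifibrotic rate, and dropout spread over 24 months. Excluding dropouts outright lowers power by about 1–3 points. The problem is an overstated power figure. It does not affect the type I error rate or the primary analysis.

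**What to change.** Replace the guarantee with what the step delivers. For example: an increase to 240 gives about 80% power for a 66.7% reduction if the one-year placebo rate is about 16% off and 8% on antifibrotics (about 10.8% in the whole placebo arm); at 12%/6% it gives about 70%, and at 10%/5% about 60–65%. In the same sentence, state which scale the 16% trigger is on.

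Add rows to Table 3 for off-antifibrotic rates of 16%, 12% and 10% at both sample sizes. By Freedman and two proportions, power at 200 is 74.6–75.9%, 62.1–63.0% and 54.4–55.0%. The figures for 240 are in the table above.

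This costs one sentence and a few table rows. It adds no participants and changes nothing in conduct; the stated power simply becomes less favourable. If the sponsor wants to keep a true 80% floor, the increase would have to depend on the observed rate, up to a stated cap. The same two methods need about 254–262 participants at 14%/7%, 298–306 at 12%/6% and 360–366 at 10%/5%.
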